### Blinding

Where possible, GPs and mental health professionals using the DMT will be blinded to the original KMMS assessment. Blinding is, however, not practical for busy, under resourced health services [34, 35]. Similarly, blinding does not always represent good care with a patient being asked to tell her story again from the beginning [36]. With respect to the ‘real world’ nature of the study many of the KMMS assessment results will be sent to the GP or mental health professional along with the KMMS referral paperwork, or the results will be viewable via the health service’s electronic medical record system. This study will monitor and assess the convergence or divergence in diagnosis of perinatal mental health disorder(s) based on the GP / mental health professional being blinded or aware of the KMMS assessment results.

### Data management

All information collected from participants is treated as strictly confidential.

Electronic data will be stored in the form of Microsoft Word, REDCap, NVivo 12 (QSR International), Microsoft Excel and Stata (StataCorp) documents. Electronic and digital audio data will be stored on a password protected computer supplied by the Rural Clinical School of Western Australia (RCSWA) or partner health service.

Once data has been obtained, collated and checked, it will be de-identified in a re-identifiable manner, with respect for the preservation of individual privacy. Medical information that is linked with a participant’s identity will not be shared with parties that do not have a direct role in health care for that participant.

Paper based consent forms will be stored under numerical code in a locked filing cabinet only accessible to study personnel. KMMS research staff will transpose any paper information to a secure database using REDCap electronic data capture tools hosted at The University of Western Australia (UWA). These data will be kept for 5 years after last access of data by the research team, after which they will be destroyed. At this time electronic data stored by the researchers will be de-identified in such a manner that it cannot be re-identified, and will be kept for a minimum of 15 years.

### Data monitoring

Data monitoring is a function of the regional Trial Management Group (TMG). This group consist of the Coordinating Principal Investigator (CPI), Research Fellow, other study staff and partner health service representatives. Data monitoring is a standing agenda item at each of the monthly TMG meetings. Any change or alteration from the procedures stated in this study protocol, consent documentation, recruitment process, or other study materials (e.g. questionnaires) are considered to be protocol deviations and will be assessed by the TMG. In the event of an unexpected adverse event related to the study or a significant protocol deviation this group would convene within 5 days to review and assess the concern. The TMG will report any concerns to the supervising Human Research Ethics Committee as per the streamlined reporting scheme recommended by the National Health and Medical Research Council (NHMRC) and Australian Health Ethics Committee [37].

The data stored on the secure REDCap database described above will be randomly assessed to make sure there are no errors in transcribing. Other data will be routinely checked by senior members of the research team.

### Data analyses

#### Quantitative analysis

KMMS validation/revalidation internal consistency of Part 1 will be determined using Cronbach’s alpha [38]. Equivalence for identifying risk of depression and anxiety compared to the DMT will be determined from receiver operating characteristic curves. Sensitivity and specificity will be determined based on these cut-points.

Differences in characteristics between antenatal and postnatal participants, participants who are or are not diagnosed with depressive and/or anxiety disorders, and participants from different regions will be compared using χ^2^ tests for categorical data and Mann–Whitney tests for continuous non-parametric data. Change in KMMS risk (from low to moderate/high, or vice versa) will be compared using McNemar’s test. Descriptive statistical analysis will be used when assessing trends and patterns in user acceptability.

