### Sample size calculation

We plan to recruit an equal number of antenatal and postnatal women. The data from antenatal and postnatal women will be pooled for the main analysis, as there was no significant difference in KMMS or study GP assessments between antenatal and postnatal participants in the Kimberley validation study [13]. If there is no significant difference between the data from the three regions, these data will also be pooled.

For the validation/revalidation study, assuming there is a minimum sensitivity of 83% for screening for perinatal depression and anxiety and prevalence is at least 25% (based on the Kimberley validation study), using calculations by Buderer [32] a sample size of 868 paired KMMS and DMT assessments will detect a two-tailed 95% CI with a maximum width of ±5% (i.e., if sensitivity 83, 95% CI 78–88%). This is at the upper end of reported sensitivities for the EPDS compared to a reference standard assessment (59–100%) [33].

Based on the Kimberley validation study [13], we expect 65% of KMMS assessments to be referred for DMT and that at least 75% of the participants who are referred will have both the KMMS and DMT assessments completed (i.e., require 1780 KMMS to obtain 868 paired assessments). For the secondary analysis to determine changes in KMMS risk, we aim to assess as many participants as possible both antenatally and postnatally. As a conservative estimate, we will assume that at least 60% of participants will have KMMS administered at both time points. Recruiting 890 antenatal women (50% of the 1780 KMMS required) should provide at least 534 paired antenatal/postnatal KMMS assessments. In addition, approximately 356 women will be recruited postnatally to ensure that we have 890 antenatal and 890 postnatal KMMS assessments required for the main sample size calculation. Therefore, we initially aimed to recruit 1246 women (890 in the antenatal period and 356 women postnatally) to provide 868 paired KMMS / DMT assessments and 534 paired antenatal/postnatal KMMS assessments.

The complexity of establishing a partnership project across three remote regional areas has taken longer than anticipated; as such a revised sample size is 700 women across all three regions. Assuming 442 of the 700 women have paired KMMS and DMT assessments, this would allow us to detect a two-tailed 95% CI with a maximum width of ±7% (i.e., if sensitivity 83, 95% CI 76–90%).

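### Mann–Whitney is named for comparing continuous data across three regions, where one three-group test is needed

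*Protocol article*

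**What the plan says.** In the protocol article, one sentence of the Quantitative analysis section assigns the same two tests to three comparisons. It opens with "Differences in characteristics between antenatal and postnatal participants, participants who are or are not diagnosed with depressive and/or anxiety disorders" and ends with "participants from different regions will be compared using χ^2^ tests for categorical data and Mann–Whitney tests for continuous non-parametric data". The next sentence names the only paired test: "Change in KMMS risk (from low to moderate/high, or vice versa) will be compared using McNemar’s test".

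The Objectives name three regions: Kimberley, Pilbara and Far North Queensland. The Sample size calculation section sets a conditional rule for them: "If there is no significant difference between the data from the three regions, these data will also be pooled". Antenatal and postnatal data are treated differently. Their pooling for the main analysis is already decided, on the results of the Kimberley validation study.

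The same section begins with "We plan to recruit an equal number of antenatal and postnatal women" and then builds in repeat assessment: "we will assume that at least 60% of participants will have KMMS administered at both time points". From this it derives that 890 antenatal women "should provide at least 534 paired antenatal/postnatal KMMS assessments", and that "approximately 356 women will be recruited postnatally to ensure that we have 890 antenatal and 890 postnatal KMMS assessments". The initial total is 1246 women. The revised target is 700 women with 442 paired KMMS and DMT assessments; how many would be seen at both time points is not restated for it.

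**The concern.** **Regions.** Mann–Whitney compares two groups. Applied to three regions it means three pairwise tests per variable, and the text names neither a global test nor a rule for multiplicity. Regional pooling depends on the absence of a significant difference, and this sentence contains the only between-region tests that the article names. If any one significant pair counts as a difference, regions that are alike will be declared different too often, and the pooled accuracy estimate may be given up without cause.

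**Antenatal versus postnatal.** The planned 890 antenatal and 890 postnatal assessments come from only 1246 women, so many women contribute to both sets. χ² and Mann–Whitney assume independent groups. If a woman seen twice is counted on both sides, the assumption fails and the tests lose sensitivity.

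**Working it through.** **1. The plan's own figures** (Sample size calculation section: sensitivity 83%, prevalence 25%, half-width 5 points, then 7).

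- Buderer: n = z² × Se(1 − Se) / (d² × prevalence) = 1.96² × 0.83 × 0.17 / (0.05² × 0.25) = 867.2, rounded up to 868. This reproduces.
- 442 pairs: half-width = 1.96 × √(0.83 × 0.17 / (442 × 0.25)) = 0.0700, or 7 points. This reproduces.
- Overlap: 0.60 × 890 = 534; 890 − 534 = 356; 890 + 356 = 1246. These reproduce.

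None of these depends on the tests at issue.

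**2. Three regions, continuous data.** The article gives no region sizes, so they are assumed here. Normal data with no regional difference were simulated 4000 times for a total of 700.

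| Assumed region sizes | Any of three pairwise Mann–Whitney tests p < 0.05 | Kruskal–Wallis p < 0.05 |
|---|---|---|
| 234, 233, 233 | 12.4% | 5.2% |
| 400, 150, 150 | 11.6% | 5.0% |

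If the three tests were independent, the figure would be 1 − 0.95³ = 14.3%. They share groups, so the true value is lower, at about 12%.

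To show what pooling is worth, assume that the 442 pairs split equally. Each region then has about 147, and the half-width for sensitivity grows from 7 to about 7 × √3 = 12 points.

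**3. Antenatal versus postnatal, if women are counted in both groups.** Shared women are 534/890 = 60% of each set, and 534/1246 = 43% of all women. With within-woman correlation ρ (assumed; the article gives none), the variance of the difference relative to independence is 1 − 0.6ρ. The independent-groups standard error is therefore too large by the factor 1/√(1 − 0.6ρ):

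- ρ = 0.3: 1/√0.82 = 1.10
- ρ = 0.5: 1/√0.70 = 1.20
- ρ = 0.6: 1/√0.64 = 1.25

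The true size of a nominal 5% test is 2 × [1 − Φ(1.96/√(1 − 0.6ρ))], which is 3.0% at ρ = 0.3 and 1.9% at ρ = 0.5. A simulation (2000 runs) with ρ set on the underlying continuous scale gave 2.8% and 1.95% for Mann–Whitney. For χ² on a 25% category it gave 3.9% and 3.4%. The error is in the conservative direction throughout.

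**The case against.** The strongest reply on regions is that the sentence condenses three comparisons, two of which have two groups, and that χ² is correct for three regions. Only continuous characteristics are affected. It is also true that the pooling rule names no test, that the primary quantitative outcome is diagnostic accuracy, and that the article nowhere says the pairwise tests would go unadjusted. These points limit the size of the finding. They do not remove it: the article names a specific test for a comparison of three groups, and that test cannot make it in one step. This is a stated method that does not fit, not a detail left to an analysis plan.

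The reply on antenatal versus postnatal is stronger, and most of it stands. A reader might infer three things that the document does not support.

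- **That an insensitive test would wrongly lead to antenatal and postnatal data being pooled.** That pooling is already fixed from the earlier study. Only regional pooling is conditional.
- **That most women sit in both groups.** The share is 60% of each set of 890 but 43% of women, and it belongs to the initial target.
- **That repeat KMMS scores will be compared as if independent.** The sentence concerns participants' characteristics, and within-woman change in risk has its own paired test, McNemar's, which is suitable. If groups are defined by period of recruitment (890 and 356), they share no women and the named tests are valid.

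Against that last reading, the stated aim of equal antenatal and postnatal numbers is met only if the 534 women count on both sides. The text leaves the matter open.

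**Conclusion.** The region point holds. For continuous variables the named test can only be run pairwise across three regions, and three unadjusted tests have a familywise error of about 12% where one global test has about 5%. The 12% assumes near-equal region sizes (11.6% under one unequal split) and no adjustment. Its bearing on regional pooling is an inference: the article makes pooling depend on significance and names no other between-region test.

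The antenatal/postnatal point is secondary and conditional. It applies only if women assessed twice enter both groups. The standard error is then about 10–25% too large for an assumed correlation of 0.3–0.6, and the tests are conservative.

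This is a minor correction. The sample sizes, the fixed antenatal/postnatal pooling and McNemar's test are unaffected.

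**What to change.** - For continuous variables across the three regions, name Kruskal–Wallis as the global test. Use pairwise Mann–Whitney only as follow-up, with a multiplicity adjustment. Keep χ² for categorical variables.
- For antenatal versus postnatal comparisons, say how women assessed at both times are handled: either use each woman's first assessment, so that the groups are independent, or use a model clustered by woman (GEE or mixed model). Keep McNemar's test for change in risk.

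The cost is a sentence or two in the Quantitative analysis section, with no new data and no change to the sample size.

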#### Qualitative analysis

User acceptability data will be descriptively and iteratively coded using NVivo11 (QSR International). The coding categories will be reviewed by the research team and Investigators before the data is thematically analysed [39]. Aboriginal and Torres Strait Islander investigators and project staff will be involved in all aspects of qualitative data coding and analysis to ensure that a cultural lens is applied in the coding and analysis of Aboriginal and Torres Strait Islander participants’ data [40–42].

Quality assessments of the KMMS and DMT as per the Quality Assessment Panel will be descriptive using the structured process identified in Additional Information 3 and 4.

The process evaluation [43, 44] will collate, assess and report on KMMS user acceptability data, KMMS quality review data, rates of KMMS and DMT completed across the regions, consultations with health service administrators and management, field notes from the research team, TMG meeting minutes, and training calendars, via the DSF.

## Discussion

The KMMS is a valid and acceptable screening tool for depression and anxiety among Aboriginal women in the Kimberley region under research conditions [13]. It has the potential to have broader geographical application for other Aboriginal and Torres Strait Islander women. Validating clinical screening tools that are acceptable to the needs and context of Aboriginal and Torres Strait Islander patients increases and informs our understanding of acceptable and culturally appropriate clinical care [17, 19, 21–25]. This project is contributing to the important public health priority of screening Aboriginal and Torres Strait Islander women for perinatal depression and anxiety with tools that are meaningful and responsive to cultural and clinical needs. This approach has the potential to improve the uptake of screening [3]. This in turn could lead to better early identification, support and treatment of mental health disorders for Aboriginal and Torres Strait Islander women [4].

Few studies have reported on the process and outcomes of clinical validation and implementation [45, 46]. Real world studies are complex, at times fragmented and require ongoing detailed planning [47–49]. High staff turnover and subsequent institutional amnesia and delays need to be factored into the planning process. Likewise the ongoing impact of colonisation, racism, different world views, cultural values and beliefs, and language need to be considered in the overall process. Real world validation and implementation studies take time and effort, and require a multidimensional and multidisciplinary approach that involves extensive consultation with heath care providers and patients. Identifying barriers and enablers in the process of real world validation and implementation studies contributes to our understanding of the complexity of improving routine clinical practice. Addressing those barriers and enablers enhances the sustainability of the clinical improvements.

## Data Availability

The datasets generated and analysed during this study will not be publicly available due to the possible identifying nature of the participants when their data is viewed in full. The Kimberley, Pilbara and FNQ regions have small populations of perinatal women and we are careful to maintain the confidentiality of our participants. Once data from the study is published, requests for additional data can be made to the corresponding author and will be assessed on grounds of reasonableness. Findings from the study will be disseminated to partners and the public via face to face meetings, plain language summaries and open access peer-reviewed journal articles.

## Abbreviations

ACCHO: Aboriginal Community Controlled Health Organisations
ACYHC: Apunipima Cape York Health Council
AHW: Aboriginal Health Worker
CHN: Child Health Nurse
DMT: Diagnosis and Management Tool
DSF: Dynamic Sustainability Framework
DSM: Diagnostic and Statistical Manual for Mental Disorders
EPDS: Edinburgh Postnatal Depression Scale
FNQ: Far North Queensland
GP: General Practitioner
KAHPF: Kimberley Aboriginal Health Planning Forum
KMMS: Kimberley Mum’s Mood Scale
MHS: Mawarnkarra Health Service
NHMRC: National Health and Medical Research Council
PAHPF: Pilbara Aboriginal Health Planning Forum
RAN: Remote Area Nurse
RCSWA: Rural Clinical School of Western Australia
TMG: Trial Management Group
WA: Western Australia
WAAHEC: Western Australian Aboriginal Health Ethics Committee
WACHS: Western Australian Country Health Service
